Taylor et al. (2000) postulated that the stress-protective effects of social support are differently utilized by men and women. Beside the fight-or-flight behaviour that may characterize the primary physiological response to stress for both males and females, behaviourally, females’ responses are more marked by a pattern of tend-and-befriend. Tending is defined as nurturing activities to protect the self and offspring, promote safety and reduce distress; and befriending as the creation and maintenance of social networks that may aid in this process. In accord to this hypothesis, interpersonal stressors like social rejection elicited higher free cortisol increases in women that in men, whereas situations involving intellectual inferiority and performance failures were perceived as more stressful by men (Stroud, Salovey & Epel, 2002).

- 1. ***Theoretical underpinning of proposed research plan***

A number of studies have shown that cognitive–behavioural stress management (CBSM) effectively reduces basal cortisol levels and/or psychological morbidity shortly after the intervention in clinical as well as nonclinical populations (HIV: Berger et al., 2008, Antoni et al., 2000, and Cruess et al., 1999; breast cancer: Cruess et al., 2000; athletes: Perna, Antoni, Kumar, Cruess, & Schneiderman, 1998). Also, in healthy participants, CBSM was observed to attenuate cortisol responses to a standardized stress test 2 weeks as well as 4 months after training (Gaab et al., 2003; Hammerfald et al., 2006).

The mentioned interventions aim to address explicit levels of self-evaluation. Individuals reflect on their experiences, evaluate the contents of consciousness, and introspect about the causes and meanings of stressful situations.

In most cases the studies were conducted with only male participants, to exclude the methodological difficulty that the intensity of endocrine response in females of reproductive age depends on the phase of the cycle and use of oral contraceptives (Kirschbaum et.al., 1999). The CBSM intervention was effective for men (Gaab et al., 2003), and when both sexes were participating, the effect of cognitive training for women was weaker (Hammerfald et al., 2006). Thus, it can be speculated that these types of stress management address rather the fight-or-flight response and might be in general more beneficial for men that for women.

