***3.2 Data analysis and sample size estimation***

Multivariate analyses of covariance and variance for repeated measures will be computed to analyse endocrine and psychophysiological stress responses as well as pre-post changes of psychometric scores between groups, controlling for differences in baseline levels when indicated. Regression analysis will be used to assess associations between psychological and cortisol parameters. For cortisol and psychophysiological parameters, areas under the response curve will be calculated with respect to increase (AUCi) and ground (AUCg), using the trapezoidal method as an indicator for the integrated biological and physiological response in the TSST (Pruessner, Kirschbaum, Meinlschmid, & Hellhammer, 2003). Data will be tested for normal distribution and homogeneity of variance using the Kolmogorov-Smirnov test and Levene’s test before statistical procedures were applied. Based on previous own studies (Gaab et al., 2003, Hammerfald et al., 2006, Storch et al., 2007), we expect a large multivariate effect size (f^2^=0.35), Therefore, the optimal total sample size of N = 48 to detect an expected large effect size of f2 = 0.35 (representing a large effect size) with a power = 0.85 and α = 0.05 was calculated a priori with the statistical software G-Power (Buchner et al., 1997). For all analyses, significance level is α = 5%. All analyses are performed according to the principle of intention to treat, with last observations carried forward when follow-up data were missing.

*Table 2: Flow through the study*

|  | TBT | WL-CC | |
| --- | --- | --- | --- |
| Baseline assessment | Advertisement with bulletins and BAPS  Information about study procedure on BAPS, screening for inclusion- and exclusion criteria on BAPS  STAI X-2, PSS, FSozU, BFW/E, ASS-SYM | | |
| Intervention | TBT | | - |
| Stress test | TSST  Assessment of 9 saliva samples -30, -20, -10, 0, 10, 20, 30, 45 and 60 min (with 0 min being directly post-TSST) for salivary free cortisol and alpha-amylase.  Continuous assessment of psychophysiological parameters (heart rate, electrodermal activity, electrocardiography, electromyography, respiratory activity and skin temperature)  Questionnaires: PASA (once), STAI X-1 | | |
| Post assessment | STAI X-2, PSS, FSozU, BFW/E, ASS-SYM | | |
| Follow-up assessment | STAI X-2, PSS, FSozU, BFW/E, ASS-SYM | | |

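### The stated power of 0.85 at N = 48 is tied to no named test: it is about 0.76 for the nine-sample multivariate group-by-time test and 0.98 for an AUC comparison

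*Protocol*

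**What the plan says.** Section 3.2 of the protocol sets out the calculation in two sentences. The effect size is introduced with "we expect a large multivariate effect size (f^2^=0.35", on the basis of the group's own earlier trials. The result is "the optimal total sample size of N = 48 to detect an expected large effect size of f2 = 0.35", "with a power = 0.85 and α = 0.05 was calculated a priori with the statistical software G-Power".

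The same section describes the analyses only by family: "Multivariate analyses of covariance and variance for repeated measures will be computed to analyse endocrine and psychophysiological stress responses", "controlling for differences in baseline levels when indicated". It adds AUCi and AUCg for cortisol and the psychophysiological parameters, and a regression: "Regression analysis will be used to assess associations between psychological and cortisol parameters". It gives no number of predictors and no number of covariates.

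Table 1 (section 3.1) makes cortisol and alpha-amylase the primary outcome, each at nine measurements. Table 2 lists them: "Assessment of 9 saliva samples -30, -20, -10, 0, 10, 20, 30, 45 and 60 min (with 0 min being directly post-TSST". There are two randomised conditions and one TSST per participant. Missing follow-up data are to be handled by carrying the last value forward. No allowance for dropout accompanies the sample size.

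**The concern.** A power figure means something only for a stated test. With f² held at 0.35, power depends strongly on the numerator df, and section 3.2 offers analyses whose df differ widely. The protocol nevertheless commits to one number and calls 48 optimal.

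If the primary test is the multivariate group-by-time test suggested by the wording and Table 1, the trial has less power than stated. If it is a comparison of AUCs, the trial has more power than stated at that f², and 48 is not the optimum. In either case a null result would be reported as coming from an 85%-powered trial, and nobody could verify that from the document.

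**Working it through.** **Inputs.** N = 48, f² = 0.35, α = 0.05 and stated power 0.85 come from section 3.2. Two groups and nine samples per marker come from section 3.1 and Tables 1 and 2. Equal allocation (24 per arm) is an assumption, since no ratio is stated. All figures are for one marker.

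**Formula.** This is the standard G-Power form for an F test of this kind. With numerator df u, denominator df v = N − u − 1 and noncentrality λ = f² × N, power = P[F′(u, v, λ) > F₀.₉₅(u, v)]. At N = 48, λ = 0.35 × 48 = 16.8.

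**Reproducing the stated figure.** Scanning u at N = 48:

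| u | v | Power at N = 48 | Smallest N for 0.85 |
|---|---|---|---|
| 1 | 46 | 0.980 | 28 |
| 2 | 45 | 0.953 | 35 |
| 3 | 44 | 0.924 | 40 |
| 4 | 43 | 0.892 | 44 |
| 5 | 42 | 0.860 | 47 |
| 6 | 41 | 0.827 | 51 |
| 7 | 40 | 0.794 | 54 |
| 8 | 39 | 0.762 | 57 |
| 9 | 38 | 0.729 | 59 |

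Under this formula the stated pair (N = 48, 0.85) matches u = 5: 47 are needed, which becomes 48 in equal arms.

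**Tests whose df the protocol fixes.**

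- Multivariate group-by-time test, two groups, nine samples: u = (2 − 1) × (9 − 1) = 8 and v = 39. The critical F is 2.187 and power is 0.762. With one to three covariates it is 0.759 to 0.754. At N = 56 power is 0.849 and at N = 57 it is 0.857, so 57 are needed, or 58 in equal arms.
- Two-group comparison of one AUC: u = 1, v = 46, power 0.980. For two equal groups f² = d²/4, so f² = 0.35 means d = 2 × √0.35 = 1.18.
- Univariate group-by-time test on nine samples, with f² on that test's own scale: at least 0.975, even at the lower-bound sphericity correction.

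None of these gives 0.85.

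**Where 5 df could come from.** A multivariate group-by-time test on the six samples from 0 to 60 min has u = 6 − 1 = 5 and power 0.860 (0.859 with one baseline covariate). A regression with five predictors also has u = 5. Section 3.2 names neither as the powered analysis.

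**Effect of loss.** At u = 5, power is 0.850 with 47 analysed and 0.840 with 46. So even on the reading that matches, 0.85 holds only with at least 47 of 48 analysed. With an assumed 43 analysed (about 10% lost), λ = 0.35 × 43 = 15.05. Power is then 0.81 for u = 5 (v = 37) and 0.69 for u = 8 (v = 34).

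**AUC comparison stated as a detectable difference.** For a two-sided t test with 24 per arm, the noncentrality is d × √(24/2). At d = 0.884 this is 3.06 on 46 df, with power 0.850.

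**The case against.** The strongest reply is that the stated figure does reproduce. Five df give 0.860 at N = 48, and other conventions also return 48. Four df with λ = f² × v gives 0.852. A repeated-measures between-group test with f = 0.35 (rather than f²), four measures and correlation 0.5 gives 0.851. A test on the six post-TSST samples is not excluded, and adjusting it for a baseline value would fit the text. This stands: there is no demonstrated arithmetic error, 5 df is not the only match, and N = 48 is not shown to be wrong.

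It is also fair that no sentence designates the 8-df test as primary. A reader might infer that the trial simply has 76% power. The document does not support that, because other analyses that fit section 3.2 have 0.86 to 0.98 or more at the same f². The 0.76 belongs to one reading. That reading is the most literal one, since the analysis and the effect size are both called multivariate and Table 1 assigns all nine samples to the primary outcome.

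A reader might also infer that f² = 0.35 is too optimistic because the section on theoretical underpinning says "when both sexes were participating, the effect of cognitive training for women was weaker". That sentence concerns cognitive training. The protocol uses it as the reason for building a different training for women, so it does not predict a weaker effect here. Whether the earlier trials support 0.35 cannot be judged from this document.

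Finally, the gap might be left to a statistical analysis plan. But the protocol itself makes the quantitative claim, so the claim should be tied to a test where it is made.

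On missing data, the carry-forward rule does not rescue the power. It is worded for follow-up data. With a single TSST, a participant who misses it has no earlier stress response to carry forward.

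**Conclusion.** The concern holds in this form: section 3.2 states a power that cannot be attached to the primary analysis, and no test whose df the protocol fixes delivers it. At N = 48, f² = 0.35 and α = 0.05, power is about 0.76 for the nine-sample multivariate group-by-time test, 0.86 for an unnamed 5-df test and 0.98 for a 1-df AUC comparison. On the first reading, 57 to 58 participants would be needed for 0.85.

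These figures rest on the standard noncentrality λ = f² × N, on equal arms, on one marker at a time, and on f² being defined on each test's own scale. The 43 analysed is an illustration, since the protocol gives no loss rate.

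**What to change.** Keep N = 48. In section 3.2, name the one test that is primary, with its effect and numerator df, and replace the power sentence with the figure for that test:

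- If the nine-sample multivariate group-by-time test is primary, state power 0.76 at f² = 0.35 (8 df).
- If a two-group AUC comparison is primary, state that 24 per arm give 85% power for a standardised difference of 0.88, two-sided 5%.
- If a 5-df analysis was intended, say which one, and state 0.86 at N = 48.

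Add the power under an assumed loss, for example with 43 analysed: 0.69 for the 8-df test or 0.81 for a 5-df test. Say how a participant without a TSST enters the primary analysis.

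The cost is one paragraph and no extra participants. The downside is a stated power that may be less favourable than 0.85.

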***3.1 Study design and data analysis***

This study is an experimental study with parallel groups. Subjects are randomized into the two conditions: Treatment condition, thus receiving tend-and-befriend training (TBT) *before* the TSST; control conditions = waitlist controls receiving tend-and-befriend training (TBT) after the termination of the study. Two weeks after the participants of the treatment condition have received the tend-and-befriend training (TBT), all participants of the treatment as well as the control condition will undergo a standardized psychosocial stress test, the Trier Social Stress Test (TSST, Kirschbaum et al., 1993). The study variables are displayed in Table 1, the flow through the study is shown in Table 2.

Table 1. Study variables

| Variables | Description | Time |
| --- | --- | --- |
| Independent Variable | Tend-and-befriend training (TBT) and waitlist control condition (WL-CC) | TBT two weeks before TSST, WL-CC after termination of study |
| Primary outcome | Cortisol and alpha-amylase | 9 measurements before, during and after TSST |
| Secondary outcomes | Psychophysiological parameters (heart rate, electrodermal activity, electrocardiography, electromyography, respiratory activity and skin temperature) | Repeated assessment before, during and after TSST |
|  | Questionnaires (PASA, STAI X-1, STAI X-2, PSS, FSozU, BFW/E, ASS-SYM) | TSST: PASA, STAI X-1  Baseline, post and follow-up: STAI X-2, PSS, FSozU, BFW/E, ASS-SYM |

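### Two unranked primary outcomes at a flat 5% allow a false primary claim about 10% of the time if either marker suffices

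*Protocol*

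**What the plan says.** Table 1 (section 3.1) lists the primary outcome as "Cortisol and alpha-amylase", timed as "9 measurements before, during and after TSST". No order, weighting or either/both rule accompanies the two markers.

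On the main analysis, section 3.2 says "Multivariate analyses of covariance and variance for repeated measures will be computed to analyse endocrine and psychophysiological stress responses", and adds "controlling for differences in baseline levels when indicated". It does not say whether the markers enter one model or two, whether the group effect or the group × time effect decides, or when baseline control is indicated.

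On summary measures it says "For cortisol and psychophysiological parameters, areas under the response curve will be calculated with respect to increase (AUCi) and ground (AUCg"). Alpha-amylase, a primary outcome, is not named there, although the secondary psychophysiological measures are.

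On error control it says "For all analyses, significance level is α = 5" per cent. The sample size rests on a single level: "we expect a large multivariate effect size (f^2^=0.35"), "with a power = 0.85 and α = 0.05 was calculated a priori", giving N = 48.

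**The concern.** With two primary outcomes and no rule for combining them, a significant result on either one can be reported as success on the primary outcome. Each test then runs at 5%, but the primary claim as a whole does not. Cortisol adds to this because section 3.2 describes it in up to three ways: the repeated-measures profile, the area with respect to increase (AUCi) and the area with respect to ground (AUCg).

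The protocol is not silent here in a way that a later analysis plan would simply complete. It fixes two primaries and a uniform 5% for all analyses, which on its face leaves no room for adjustment. A choice among markers and summaries made after the data are seen would carry little weight.

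**Working it through.** **The plan's own figure.** The protocol states no error rate for the primary claim as a whole; its only derived figure is N = 48. With the noncentral F distribution, λ = f²N, f² = 0.35, degrees of freedom u and N − u − 1, α = 0.05 and power 0.85, the required N is 28 (u = 1), 35 (u = 2), 40 (u = 3), 44 (u = 4), 47 (u = 5) and 51 (u = 6). At N = 48 and u = 5 the power is 86.0%. So 48 fits about five numerator degrees of freedom, but the protocol names neither the test nor u, and the figure cannot be firmly reproduced. What is clear is that α = 0.05 was entered once, with no division between two markers.

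**Inputs for the error rate.** From the protocol: two primary markers, 5% per analysis, and AUCi and AUCg for cortisol only. Assumed, because not stated: two-sided tests, 24 per arm, either marker sufficient, separate tests, and correlation between tests varied over a range.

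**Two markers, one test each.**
- Independent: 1 − (1 − 0.05)² = 1 − 0.9025 = 9.75%.
- Correlated test statistics (simulated bivariate normal): 9.6% at 0.2, 9.1% at 0.5, 8.3% at 0.7.

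**Cortisol AUCs added as between-arm tests.** This makes four tests: cortisol profile, AUCi and AUCg, and the alpha-amylase profile.
- Independent: 1 − 0.95⁴ = 1 − 0.8145 = 18.5%.
- Correlated within cortisol (simulated multivariate normal, correlation across markers 0 to 0.2): about 17% at 0.5, 15% at 0.7, 13% at 0.9.
- Direct null simulation: 18.4%. It used 20,000 trials, 24 per arm, the nine protocol sampling times, an assumed correlation of 0.4 + 0.6·exp(−lag/30 min), independent markers, a Hotelling group × time test, and t tests on the AUCs.

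**Readings that hold 5%.**
- Both markers must be positive, one test each: 0.05² = 0.25% if neither marker is affected and the tests are independent; at most 5% if only one is truly affected.
- One joint test of both markers decides: 5%.

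**After correction.**
- Both markers at 0.05/2 = 0.025: 1 − 0.975² = 4.94% if independent.
- Power at N = 48 when a marker is tested at 0.025 instead of 0.05, with f² = 0.35:

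| u | Power at 0.05 | Power at 0.025 | N for 85% at 0.025 |
|---|---|---|---|
| 1 | 98.0% | 95.9% | 34 |
| 2 | 95.3% | 91.5% | 41 |
| 5 | 86.0% | 77.8% | 55 |

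**The case against.** **The inflation is conditional.** Section 3.2 speaks of multivariate analyses and a multivariate effect size, and Table 1 has one primary-outcome row. A joint test, or a requirement that both markers respond, would keep the error at or below 5%. This stands as a condition on the size, but it does not remove the point. Multivariate may refer only to the nine time points; the same sentence also covers psychophysiology and questionnaires, and neither rule is written.

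**The AUCs may not be tests.** The protocol says only that they will be calculated, as indicators of the integrated response, directly after a sentence on regression of psychological and cortisol parameters. No between-arm AUC test is stated. This stands: the firm count is one test per marker, and 18.5% applies only if the AUCs are also compared between arms.

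**A reader might infer a rate near 26%.** Six independent tests would give 1 − 0.95⁶ = 26.5%. But three tests per marker would include alpha-amylase AUCs, which section 3.2 does not plan. Counting group and group × time effects separately for both markers, plus the two cortisol AUCs, also makes six tests (23.0% in the same null simulation), but the protocol does not commit to that. Nor does the protocol promise a 5% rate for the trial as a whole: it sets a level per analysis.

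**Multiplicity rules often sit in the analysis plan, and section 5 calls this basic research.** Silence alone would not be a finding. Here, however, the protocol states a flat 5% and two unranked primaries. It is also a randomised evaluation with a declared primary outcome and an a priori power calculation.

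**Conclusion.** The point holds in a bounded form. If either marker can carry the primary claim and each is tested once at 5%, the chance of a false primary claim is about 10%: 9.75% under independence, and about 8 to 9% at correlations of 0.7 to 0.5. If cortisol AUCi and AUCg also serve as between-arm tests, it is at most about 18.5%, and about 13 to 17% when the cortisol tests correlate at 0.9 to 0.5. Both figures rest on the either-marker reading, which the protocol permits but does not state. A deciding joint test, or a rule that both markers must be positive, would hold it at or below 5%. A figure near 26% is not supported for the plan as written.

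**What to change.** In Table 1 and section 3.2:

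1. Name one decisive between-arm test per marker, for example the planned repeated-measures group × time test or one named AUC. Which of these is chosen matters less than fixing it in advance.
2. Then choose one rule:
   - Cortisol as the single primary at two-sided 5%, with alpha-amylase tested at 5% only if cortisol is significant. The rationale in sections 1 and 2 centres on the HPA axis, section 3.5 treats cortisol as its leading marker, and alpha-amylase is not named in the background.
   - Holm across the two markers: the smaller p-value against 0.025 and, if that is significant, the larger against 0.05.
3. Label the remaining cortisol summaries as secondary, and limit the flat 5% statement to analyses outside this primary family.

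Cost: wording only, plus a trade-off. Under the fixed order, alpha-amylase loses its stand-alone confirmatory status, and multiplicity calls for no change in N. Under Holm both markers keep their standing but some power is lost. At the first step with N = 48, the loss is about 2 points if the test has one numerator degree of freedom (98.0% to 95.9%) and about 8 points if it has five (86.0% to 77.8%). The protocol should therefore also name the test behind its sample size.

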All personal data will be handled securely according to Swiss Data Protection Regulation. The subject’s data will be coded. A code will be attributed to each subject and will be saved in digital form. The codes can be provided to the Ethics Committee at any time. Only the scientific staff involved in this study will have access to the collected data.

*Direct consequences for the involved participants*

This study has to be considered as basic research with pure scientific interest. The study is of no direct benefit for the volunteers. Participants receive either a financial (CHF 50) or administrative (5 "Versuchspersonenstunden" as part of their Bachelor studies) reimbursement.

The participants will be exposed to the TSST, which is an unpleasant and stressful situation. However, the TSST has been used in different healthy and patient population and so far, no intermediate or long-term negative consequences have been published. Also, the TSST has been used at the Department of Psychology and by the primary investigator (JG) many times. Additionally and most importantly, volunteers can stop TSST themselves at any time during each experimental run, without negative consequences. Therefore, the risks for the participants are considered as low. The benefit of the study is that participants receive tend-and-befriend training (TBT) at no costs. Also, participants will repeatedly be questioned about their personality traits and well-being with different questionnaires. There are no known negative effects of that kind of interrogation. The participants are informed about the whole procedure and potential risks. A written consent will also be signed before entering the study. The written consent explains the goals and risks of the study and clarifies that the participants have the right to end the study whenever they want.

1. **Documentation of the data, quality control and quality assurance**

The original data concerning the study are accessible for audits of the respective ethics committee. These inspections are conducted according to the legal conditions of data protection. The case report forms contain information about every single subject participating in the study. Data will be stored at the Department of Psychology for 10 years.

*6.1 Budget*

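### Last observation carried forward is a poor rule for the repeated questionnaires and gives no value for women who miss the only TSST, so the promised intention-to-treat primary analysis is an analysis of women tested

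*Protocol*

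**What the plan says.** Protocol section 3.2 sets the analysis principle and the missing-data rule in one sentence: "All analyses are performed according to the principle of intention to treat, with last observations carried forward when follow-up data were missing".

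Table 1 (section 3.1) gives the primary outcome, cortisol and alpha-amylase, as "9 measurements before, during and after TSST". Section 3.1 describes one stress test, two weeks after the training: "all participants of the treatment as well as the control condition will undergo a standardized psychosocial stress test". Table 2 places all saliva sampling in that session: "Assessment of 9 saliva samples -30, -20, -10, 0, 10, 20, 30, 45 and 60 min". No saliva is collected before it. The psychophysiological measures, PASA and STAI X-1 also belong to this one session.

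Only the remaining questionnaires have several occasions: "Baseline, post and follow-up: STAI X-2, PSS, FSozU, BFW/E, ASS-SYM". Section 3.5 dates the follow-up at 4 weeks after the intervention.

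Women may leave the study at any time (section 3.3). The section on ethical aspects adds that "volunteers can stop TSST themselves at any time during each experimental run". Section 3.2 gives a total of N = 48 and no dropout allowance.

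**The concern.** The sentence promises that every analysis keeps every randomised woman, and offers one device for doing so. The device needs an earlier value of the same variable. The repeated questionnaires have one; the primary outcome does not, for a woman who never attends the TSST. She leaves the primary comparison although the plan calls it intention to treat.

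Loss before the TSST could differ by arm, because only the training arm has sessions to attend beforehand: 4 + 2 + 2 + 2 + 2 + 4 = 16 hours according to the attached manual. If the women who drop out differ in stress reactivity, the comparison of those tested is no longer protected by randomisation.

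Where the device does work, it replaces an unknown score with an old one and counts it as data. At stake are the size and precision of the questionnaire effects, and an accurate description of who is in the primary analysis.

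**Working it through.** **1. Which outcomes have a value to carry?**

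| Outcome | Occasions | Earlier occasion available? |
|---|---|---|
| STAI X-2, PSS, FSozU, BFW/E, ASS-SYM | baseline, post, follow-up | yes |
| Cortisol, alpha-amylase | one TSST, nine samples | no, if the session is missed |
| Psychophysiology, PASA, STAI X-1 | the same TSST | no, if the session is missed |

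**2. Questionnaires.** Assumptions, none from the protocol: the training arm truly changes by D, the waitlist arm does not change, a share d of the training arm only is missing, and the missing women would have changed like the others.

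- Baseline carried forward: estimate = (1 − d) × D. This is 0.90D for d = 0.10 and 0.80D for d = 0.20, against a true D.
- Post score carried to follow-up, effect halved by then: estimate = (1 − d) × 0.5D + d × D. This is 0.55D for d = 0.10 and 0.60D for d = 0.20, against a true 0.50D. With D = 0.6 SD and d = 0.20: 0.8 × 0.3 + 0.2 × 0.6 = 0.36 SD against 0.30 SD, or 20% too large.
- Post score carried, effect persists: estimate = D, no bias.

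The bias can therefore be downward, upward or nil. In each case the filled-in scores enter the standard error as if they had been measured.

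**3. Primary outcome, TSST missed.** There is nothing to carry, so the analysed number is N × (1 − d). The stated N = 48 (f² = 0.35, power 0.85, α = 0.05) does not say how many terms are tested. Using the noncentral F with λ = f² × N, df1 = k and df2 = N − k − 1, k = 5 requires N = 47 (48 for equal arms) and gives power 0.86 at 48; k = 4 requires 44 and k = 6 requires 51. Taking k = 5 as an assumption:

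| Assumed loss | Women tested | Power |
|---|---|---|
| 0% | 48 | 0.86 |
| 5% | 46 | 0.84 |
| 10% | 43 | 0.81 |
| 20% | 38 | 0.74 |

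**4. Primary outcome, partial saliva series, if the rule were read as applying there.** Assumed cortisol curve at the nine stated times: 5, 4.8, 5, 8, 12, 11, 9, 7, 5.5. By the trapezoidal rule:

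AUCg = 49 + 49 + 65 + 100 + 115 + 100 + 120 + 93.75 = 691.75

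AUCi = 691.75 − 5 × 90 = 241.75

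| Last sample (min) | AUCi after carrying forward | Ratio to true |
|---|---|---|
| −10 | −2 | −0.01 |
| 0 | 193 | 0.80 |
| +10 | 413 | 1.71 |
| +20 | 368 | 1.52 |
| +30 | 298 | 1.23 |
| +45 | 253 | 1.05 |

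The direction depends on where sampling ends, and the error is small late in the session. If there were no training effect and 20% of the training arm had no sample after −10, its mean AUCi would be 0.8 × 241.75 + 0.2 × (−2) = 193.0, a spurious reduction of about 20%.

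**The case against.** The strongest reply is that the carry-forward clause concerns follow-up data, and follow-up is a named questionnaire occasion in Tables 1 and 2, separate from the stress test. On that reading the rule was never meant for saliva, and handling of a missed TSST may be left to a SAP that is not at hand. The reading is plausible, and for that reason step 4 is conditional. It does not remove the point: the same sentence claims intention to treat for all analyses, and the single-occasion design cannot deliver that for women who are not tested. The questionnaire rule is also stated outright rather than deferred.

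A reader might go further in four ways that the protocol does not support.

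- *The rule cannot be carried out for the primary outcome at all.* It can be computed for a partial series; it fails only when the whole session is missing.
- *It gives wrong values wherever it is used.* Step 2 shows a case with no bias, and step 4 shows little error when only the last sample is missing.
- *A woman who stops the TSST is scored as a non-responder.* The protocol lets her stop the test but does not say that saliva sampling then ends. She could still give the samples from 0 to +60 min.
- *Loss will be heavier in the training arm.* The 16 hours make this possible, but the protocol gives no dropout figure. Waitlist women, whose training comes only after the study ends, may also leave.

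It is also fair to say that no method recovers much for a woman without a TSST. A mixed model has no outcome data from her, and imputation has no earlier cortisol or amylase value to work from. That limit comes from the design, not from the carry-forward rule.

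**Conclusion.** The point holds in two parts. For the five repeated questionnaires, the stated rule is a single imputation that assumes no change after the last score and understates uncertainty. Its bias can run either way: under the assumptions in step 2 it ranges from none to 20% of the true effect in either direction at 20% one-sided loss. For the primary outcome, the rule provides no value for a randomised woman who misses the only TSST, so the analysis called intention to treat is one of women tested. That calls for an accurate description and reporting of the loss by arm; it does not show the primary comparison to be invalid.

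The cortisol curve, the dropout rates, the decay of effect and k = 5 are all assumptions. The conclusions that do not depend on them are the absence of any saliva value before the TSST session and the treatment of carried-forward scores as observed.

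**What to change.** Before the data are analysed, amend section 3.2 as follows.

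- Delete the carry-forward rule.
- Analyse the repeated questionnaires, and any partial saliva series, with a likelihood-based mixed model with arm, time and arm-by-time terms, using all observed values and the randomised arm. This assumes that data are missing at random given what was observed. An unstructured covariance for nine samples has 9 × 10 / 2 = 45 parameters, so name a more parsimonious structure for the saliva data.
- Describe the primary analysis as all randomised women with TSST data, analysed by randomised arm, and report the number without a TSST in each arm.
- Add one sensitivity analysis for women without a TSST, for example multiple imputation with a delta adjustment, and present it as a test of robustness rather than as recovered information.

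The cost is a few lines of text, slightly more programming, and slightly wider intervals for the questionnaires.
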